## **5.5. Reporting and review of the results**

The results of the interim analysis will be submitted to the Data and Safety Monitoring Committee by the Data Center as an Interim Analysis Report and reviewed for the acceptability of continuation of the study and for publication of the results. The Data and Safety Monitoring Committee considers whether to continue the study at the meeting and recommends whether to continue the study and whether to inform the results to principal physician or group chair based on the results of the review.

Members of the Data and Safety Monitoring Committee of the relevant groups are not included in the review. Unless the results of the interim analysis make recommendations for discontinuation of the study from the Data and Safety Monitoring Committee, the research representative, research office, participating institution researchers, group representatives, and group secretaries of the study will not be able to know the results of the interim analysis until the final follow-up is completed.

When the Interim Analysis Report has been reviewed by the Data and Safety Monitoring Committee to recommend termination or change of all or part of the study, the principle investigator and group chair review the recommendations and decide whether to discontinue or change some of the study.

If the study is discontinued or part of the study is changed, the principal investigator and group chair shall submit in written form a request to the Data and Safety Monitoring Committee for permission to discontinue the study or a request to revise the protocol. Following approval by the Data and Safety Monitoring Committee, the principal investigator may discontinue the study or change part of the study.

The Study Chair and Group Chair can disagree with the recommendations of the Data and Safety Monitoring Committee, but if they fail to coordinate their opinions with the Data and Safety Monitoring Committee, they will ultimately follow the instructions of JCOG Chair.

If the study is terminated, the subsequent follow-up period will be 1 years from the date of last registration.

If the interim analysis resulted in study termination, the interim analysis will be the primary analysis of the study. The Data Center, in cooperation with the Research Representative Physicians and Research Secretariat, will conduct the analysis required to complement the incomplete data and publish the results, focusing on the results of the interim analysis, and promptly prepare the Major Analysis Report and submit it to the Group and the Data and Safety Monitoring Committee.

## **6. Final analysis**

### **6.1. The timing**

The final analysis will be performed one year after accrual completion.

### **6.2. Analysis methods**

The same as those detailed in Section 2 to 4 in the SAP.

## 7. Planned accrual, accrual period, and follow-up periods

As described in "Section 2.4.2. in the protocol. Based on the background presented in Clinical Hypothesis and Rationale for Number of Enrollment", we assume a median survival of 8 and 12 months (HR=0.67) for inferior and superior treatment groups. Total of 63 patients per group and 126 patients in both groups (114 events required) will be required using the method of Schoenfeld and Richter. The above calculation assumes 6 years of enrollment, 1 year of follow-up,  $\alpha = 10\%$  (two-sided), and 70% power. The required number of patients and events are listed in table below when median survival time of arm A is different to the expectation.

Table: Number of Analyses Required (Number of Events Required)

| Median Survival
(mo) | Power    |          |          |          |
|-------------------------|----------|----------|----------|----------|
|                         | 65%      | 70%      | 75%      | 80%      |
| 7.0 vs. 10.5            | 108(100) | 124(114) | 142(131) | 162(150) |
| 8.0 vs. 12.0            | 112(100) | 126(114) | 144(131) | 166(150) |
| 9.0 vs. 13.5            | 114(100) | 130(114) | 148(131) | 170(150) |

※ Number of required events in parentheses

Based on these, the following will be established in view of some cases of loss to follow-up.

Planned enrollment: 70 patients in each group and 140 patients in both groups

Enrollment period: 6 years, follow-up period: 1 year after completion of enrollment

Consider sample size recalculation (SSR) if the prognosis is obviously better than assumed, or if 70 or more patients are enrolled within first 2.5 years. The SSR needs reconsideration of clinically meaningful differences in a blinded fashion and needs to be performed prior to the conduct of the primary analysis.

<Additions in protocol ver. 1.1>

The registration pace after the enrollment start was smooth and exceeded the plan, and 70 cases were enrolled in October, 2016, when 2 years and 2 months passed from the enrollment start, which met the above-mentioned criteria for SSR. SSR with an aim of raising power to 80% was accepted at the meeting of the Hepatobiliary and Pancreatic Group on October 29, 2016, the group meeting of the Esophageal Cancer Group on November 19, 2016, and the group meeting of the Gastric Cancer Group on January 7, 2017. Therefore, the required number of enrollment was changed to 170. In addition, the "1-year analysis period" was added to the study period, and the following changes were made.

Planned enrollment: 85 patients in each group and 170 patients in both groups

Enrollment period: 6 years;

Follow-up period: 1 year after completion of enrollment;

Analysis period: 1 year;

Total study period: 8 years

## 8. Software

SAS 9.4

## **Supplemental note for the first interim analysis (2017/9)**

<Data sets for the analysis (see Section 5.2 in the SAP)>

Data sets used for the first half year of 2017 fiscal year semi-annual monitoring report is used.

<Population for primary analysis (see Section 2 in the SAP)>

OS and PFS are analyzed for all the 86 patients enrolled until March 31, 2017. For response rate, only 46 patients are analyzed among 79 patients with measurable disease. This is because some patients are under treatment and thus CRF regarding response evaluation is not submitted. Note that CRFs of the 46 patients have been submitted and the associated queries have been resolved.

<Population for safety analyses (see Section 3 in the SAP)>

Of the 86 patients enrolled until March 31, 2017, safety analyses are performed on 72 patients whose CRF for treatment are collected by March 31, 2017. In the interim analysis, the results of safety analysis are presented using the first half year of 2017 fiscal year semi-annual monitoring report.

<Population for the other analysis (see Section 4 in the SAP)>

Dose intensity of cisplatin is not analyzed at the timing of interim analysis.

<Information time>

Among the 86 patients for the efficacy population, the number of observed events is 55 in total. Thus, the information time at the 1st interim analysis is 55/150 (0.3666666666666666600). The calculated significance level and boundary are as follows.

- Two-sided significance level:  $\alpha' = 0.0024177822594063$
- Boundary for log-rank test statistic =  $\pm 3.0334456905510900$

<Items to be reported in the interim analysis report>

- Primary endpoint: OS
  - Interim analysis methods and decision rules
    - Summary of decision rules in the interim analysis and the significance level.
  - Kaplan-Meier curves for OS
    - Group comparisons
    - Kaplan-Meier curves in the subgroups of randomization adjustment factors.
  - Summary statistics
    - Sample size, number of events, median OS and the 95% confidence interval, 1-year OS and the 95% confidence interval
    - The above summary statistics in the pooled survival curve
    - The above summary statistics in the survival curves of subgroups regarding randomization adjustment factors
  - The primary analysis results for evaluating a stop for efficacy
    - Results of stratified log-rank test for superiority hypothesis
    - Results of unstratified log-rank test for superiority hypothesis
    - Hazard ratio and the  $(1-2\alpha')$ -% confidence interval constructed from stratified Cox regression model
    - Hazard ratio and the  $(1-2\alpha')$ -% confidence interval constructed from unstratified Cox regression model
  - Supporting information to evaluate a stop for inefficacy
    - Predictive probabilities defined in the Section 5.4 in the SAP.
    - Conditional power defined in the Section 5.4 in the SAP.
- Secondary endpoint: PFS
  - Kaplan-Meier curves for PFS

- Summary statistics
  - Sample size, number of PFS events, median PFS and the 95% confidence interval, 1-year PFS and the 95% confidence interval
  - The above summary statistics in the pooled survival curve
- The results of unstratified log-rank test
- Hazard ratio and the 95% confidence interval constructed from unstratified Cox regression model
- Secondary endpoint: response rate
  - Best responses in the two groups
  - Response rates in the two groups with corresponding exact 95% confidence intervals
    - Two-sided p-value is also calculated using Fisher's exact test.

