## **1. Key decision criteria and multiplicity adjustment**

### **1.1. Key decision criteria for study results**

The purpose is to test whether one of the two deemed standard-of-care arms A (EP-therapy) and B (IP-therapy) outperforms the rest regarding the primary endpoint, overall survival.

We conclude that EP therapy is a more useful treatment when the two-sided p-value is less than 10% and the survival curve of EP therapy exceeds that of IP therapy. Meanwhile, we conclude that IP therapy is a more useful treatment when the two-sided p-value is less than 10% and the survival curve of IP therapy exceeds that of EP therapy. If the difference was not significant at a two-sided significance level of 10%, one of the two deemed standard treatment cannot be judged to be more useful. In this case, we conclude that both regimen continue to be the standard of care, as there is no evidence to actively recommend either one of them.

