### **1.2. Multiplicity Adjustment**

For a reason that our primary interest is whether either of two arms is superior to the other, two-sided test is used. The study-wise significance level is set at two-sided 10%. In the primary analysis, two-sided 90% confidence intervals corresponding to a two-sided 10% significance level will be calculated, and in the other analyses, two-sided 95% confidence intervals will be calculated for descriptive purposes.

Significance levels and corresponding confidence coefficients used to test the primary hypotheses are based on the multiplicity adjustment associated with the interim analysis.

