### 5.3. Multiplicity adjustment methods in interim analyses

Interim analysis will be conducted by the JCOG Data Center. To control the study-wise type-I error rate at 10%, the multiplicity of the interim and final analyses is adjusted using Lan & DeMets's alpha spending functions, and the calculated statistical significance level is used for testing primary endpoint between arms. As alpha spending functions, we use O'Brien & Fleming type.

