### 5.4. Decision Criteria in the interim analysis

Decision criteria based on the results of the interim analysis is following.

- If superiority of arm B over arm A (or vice versa) is demonstrated based on a criterion that the two-sided p-value calculated from stratified log-rank test is below the significance level calculated from the method detailed in Section 5.3, then the study is to be discontinued due to an efficacy.
- Otherwise, the study is to be discontinued.

Futility stop is also considered from various aspects. As a reference, the following is calculated.

- Predictive probability for primary endpoint (based on Spiegelhalter et al. (1992)) that will be calculated based on a Bayesian predictive distribution of hazard ratio on the final analysis. To calculate the following predictive probabilities, log-rank score statistic calculated from the stratified log-rank test for overall survival (in the primary analysis) is used.
  - Predictive probability that the superiority of arm B over arm A (or vice versa) will be demonstrated on the final analysis (at the time of information time=1).
  - Predictive probability that point estimate of hazard ratio for arm A will be greater than one on the final analysis (at the time of information time=1).
  - Predictive probability that point estimate of hazard ratio for arm B will be greater than one on the final analysis (at the time of information time=1).
- Conditional power for primary endpoint (based on Halperin et al. (1982)). To calculate the following conditional power, log-rank score statistic calculated from the stratified log-rank test for overall survival (in the primary analysis) is used.

- Conditional power given the observed interim analysis data that the trial would reject the null hypothesis on the final analysis assuming the true hazard ratio for arm A after 1st interim analysis would be one (the null hypothesis for the primary analysis)
- Conditional power given the observed interim analysis data that the trial would reject the null hypothesis on the final analysis assuming the true hazard ratio for arm B after 1st interim analysis would be one (the null hypothesis for the primary analysis)
- Conditional power given the observed interim analysis data that the trial would reject the null hypothesis on the final analysis assuming the true hazard ratio for arm A after 1st interim analysis would be 0.67 (the expected hazard ratio for overall survival)

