## **Supplemental note for the final analysis (2021/6)**

<Data sets for the analysis (see Section 5.2 in the SAP)>

Data sets based on a follow-up survey on March, 2021.

<Population for primary analysis (see Section 2 in the SAP)>

OS and PFS are analyzed for all enrolled 170 patients. As supportive analysis for OS and PFS, two analysis populations (all eligible 166 patients and 152 patients eligible for centrally pathological review) are also analyzed. Response rate is analyzed for 157 eligible patients with measurable disease.

<Population for safety analyses (see Section 3 in the SAP)>

Safety analyses are performed on 164 eligible and treated patients.

<Information time>

Among the 170 patients for the efficacy population, the total number of observed events was 55 at the timing of interim analysis and that is 151 in the final analysis. Thus, the information time, the calculated significance level, and boundary in the interim and final analyses are as follows.

- The interim analysis
  - Information time: 55/150 (0.36666666666666600)
  - Two-sided significance level:  $\alpha' = 0.0024177822594063$
  - Boundary for log-rank test statistic =  $\pm 3.0334456905510900$
- The final analysis
  - Information time: 1.00 (all the remaining alpha level is spent)
  - Two-sided significance level:  $\alpha' = 0.0992019861996200$
  - Boundary for log-rank test statistic =  $\pm 1.6487347573298200$

<Adjustment factors>

The primary analysis (stratified log-rank test) for overall survival is planned to use a randomization adjustment factor of primary organ (gastrointestinal vs. hepatobiliary-pancreatic). For a reason that the number of deaths is enough for each stratum in the adjustment factor, the stratified log-rank test uses the adjustment factor as planned.

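### The interim hazard-ratio intervals are set at 1−2α' although α' is already a two-sided level, so they are about 7% too narrow on the log scale

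*SAP*

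**What the plan says.** Three places in the SAP bear on the interim interval.

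- **Supplemental note for the first interim analysis, Information time.** At 55 of 150 events the note gives "\alpha' = 0.0024177822594063", labels it two-sided, and pairs it with a log-rank boundary of ±3.0334.
- **Same note, items to be reported.** Among the overall survival results meant for judging an efficacy stop, it lists the hazard ratio with a "1-2\alpha')$ -% confidence interval constructed from stratified Cox regression model". The next line asks for the same coefficient from the unstratified Cox model.
- **Section 5.4.** The study stops for efficacy if "the two-sided p-value calculated from stratified log-rank test is below the significance level calculated from the method detailed in Section 5.3". No confidence interval enters this rule.

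Section 1.2 sets the convention that links test and interval: in the primary analysis, "two-sided 90% confidence intervals corresponding to a two-sided 10% significance level will be calculated". That is coefficient 1−α for a two-sided α. The section then adds that both the levels and the confidence coefficients for the primary hypothesis follow the interim multiplicity adjustment.

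**The concern.** For a two-sided level α', the interval that excludes 1 when the test rejects has coefficient 1−α'. The coefficient 1−2α' belongs to a level defined on one side. The note labels α' two-sided and then treats it as one-sided when it sets the interval.

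This matters because the intervals stand with the results used to assess an efficacy stop and go to the Data and Safety Monitoring Committee in the Interim Analysis Report. An interval that carries the interim α' but is too narrow can exclude 1 next to a log-rank test that has not crossed its boundary. The committee would then hold two results that look alpha-adjusted and disagree, for no reason other than the wrong coefficient.

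**Working it through.** **Inputs from the SAP.** Study-wise level 10%, two-sided (Section 1.2). Lan-DeMets spending: "As alpha spending functions, we use O'Brien & Fleming type" (Section 5.3). Information time t = 55/150 = 0.3667, α' = 0.0024178, boundary ±3.0334 (interim note). Design medians 8 and 12 months, so a hazard ratio of 8/12 = 0.667 (Section 7).

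**Assumption.** SE(log HR) = 2/√55 = 0.2697, which presumes a near-equal split of the 55 events between arms. The SAP gives no standard error.

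**1. Reproduce the SAP's figures and check that α' is two-sided.** With 5% spent on each side,

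α'(t) = 4[1 − Φ(z₀.₉₇₅/√t)] = 4[1 − Φ(1.960/0.6055)] = 4[1 − Φ(3.2368)] = 0.0024178.

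This agrees with the SAP. The matching critical value is z(1 − α'/2) = 3.0334, the stated boundary. So α' is two-sided by calculation as well as by label.

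**2. Compare the two coefficients.** The hazard-ratio limits are exp(±multiplier × 0.2697).

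| | As written, 1−2α' | Matching the test, 1−α' |
|---|---|---|
| Coefficient | 1 − 0.0048356 = 99.52% | 1 − 0.0024178 = 99.76% |
| Multiplier | z(1−α') = 2.8178 | z(1−α'/2) = 3.0334 |
| Half-width on log scale | 0.760 | 0.818 |
| Excludes 1 at HR below | 0.468 | 0.441 |
| or above | 2.138 | 2.266 |

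The width ratio is 2.8178/3.0334 = 0.929, so the written interval is about 7% too narrow on the log scale.

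**3. How often interval and test would disagree.** They disagree when 2.818 < |Z| < 3.033.

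- Under the null: 2α' − α' = α' = 0.0024, or 0.24%.
- Under HR 0.667: the mean of Z is 0.4055/0.2697 = 1.503 in absolute value. The probability is Φ(1.503 − 2.818) − Φ(1.503 − 3.033) = 0.031, about 3%.

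**4. Check against the SAP's own convention.** Section 1.2 pairs 10% two-sided with 90%, which is 1−α. Applying 1−2α' to the final two-sided level of 0.0992 would give 1 − 0.1984 = 80.2%. The SAP does not ask for that; it only shows that the interim formula cannot be reconciled with Section 1.2.

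**5. Check the final level.** The stated boundaries, ±3.0334 at the interim and ±1.6487 at the final analysis, with correlation √(55/150), give a total two-sided crossing probability of 0.1000. The final level of 0.0992 is therefore correct, with the interim alpha deducted.

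**The case against.** The strongest reply is that the interval decides nothing. Section 5.4 rests stopping on the stratified log-rank p-value alone, and the committee receives that result and the significance level in the same report. The zone of disagreement is small. Even at matched levels a Cox interval and a log-rank test can differ slightly. The unstratified Cox interval has no matching stopping test, so the argument that interval and stopping rule conflict applies properly to the stratified line only. The note dates from 2017, and the trial went on to 170 patients and a final analysis.

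All of this stands, and it limits the consequence to reporting. It does not make the coefficient right: 1−2α' contradicts both the two-sided label in the same note and Section 1.2.

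A reader might infer two stronger points, and the SAP supports neither.

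- **That the interim error is doubled, to 2α' = 0.48%.** That would be the error rate only if the interval were used as the stopping test, and it is not.
- **That the 10% rule in Section 1.1 and the 90% interval in Section 1.2 ignore the alpha already spent.** An unadjusted 10% at the final analysis would give a total error of 10.08%, but the SAP does not plan that. Section 1.2 makes levels and coefficients follow the adjustment, Section 5.3 applies the calculated level to the primary endpoint, and the final-analysis note fixes "\alpha' = 0.0992019861996200".

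**Conclusion.** The coefficient is wrong as written in both Cox lines of the interim note. The interval that corresponds to the stated two-sided level is 99.76%, and the SAP asks for 99.52%.

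The label, the reproduced boundary and Section 1.2 all lead to this conclusion, and it needs no assumption. The hazard-ratio thresholds and the figure of about 3% do rest on the near-equal event split and would shift somewhat with the actual standard error. The 7% narrowing and the 0.24% under the null do not depend on the split.

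The stopping rule, the type I error and the final analysis are unaffected.

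**What to change.** - In the supplemental note for the first interim analysis, replace (1−2α') with 100(1−α')%, that is 99.76%, in both the stratified and the unstratified Cox line.
- If the interim report gave intervals at 99.52%, correct them or add a note stating the coefficient used and the 99.76% limits.
- Optional: in Section 1.1, add a cross-reference to the adjusted level in Section 1.2. A reference is better than a number there, because 0.0992 depends on the information time observed at the interim analysis.

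The cost is two lines of text and one option in the Cox program. The interim intervals become slightly wider, and no decision rule or final result changes.

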## **Supplemental note for the final analysis (2021/6)**

<Data sets for the analysis (see Section 5.2 in the SAP)>

Data sets based on a follow-up survey on March, 2021.

<Population for primary analysis (see Section 2 in the SAP)>

OS and PFS are analyzed for all enrolled 170 patients. As supportive analysis for OS and PFS, two analysis populations (all eligible 166 patients and 152 patients eligible for centrally pathological review) are also analyzed. Response rate is analyzed for 157 eligible patients with measurable disease.

<Population for safety analyses (see Section 3 in the SAP)>

Safety analyses are performed on 164 eligible and treated patients.

<Information time>

Among the 170 patients for the efficacy population, the total number of observed events was 55 at the timing of interim analysis and that is 151 in the final analysis. Thus, the information time, the calculated significance level, and boundary in the interim and final analyses are as follows.

- The interim analysis
  - Information time: 55/150 (0.36666666666666600)
  - Two-sided significance level:  $\alpha' = 0.0024177822594063$
  - Boundary for log-rank test statistic =  $\pm 3.0334456905510900$
- The final analysis
  - Information time: 1.00 (all the remaining alpha level is spent)
  - Two-sided significance level:  $\alpha' = 0.0992019861996200$
  - Boundary for log-rank test statistic =  $\pm 1.6487347573298200$

<Adjustment factors>

The primary analysis (stratified log-rank test) for overall survival is planned to use a randomization adjustment factor of primary organ (gastrointestinal vs. hepatobiliary-pancreatic). For a reason that the number of deaths is enough for each stratum in the adjustment factor, the stratified log-rank test uses the adjustment factor as planned.

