#### **3.1. Proportion of patients with adverse events**

The proportion is calculated to evaluate differences in toxicity among the two groups. Frequency of adverse events marking the worst grade in CTCAE v4.0-JCOG that occurred during the entire course of therapy will be calculated (by group) using the number of all treated patients as a denominator. If necessary, exact confidence intervals will be calculated and Fisher's exact test will be used for group comparisons.

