#### **3.2. Proportion of patients with serious adverse events**

Grade 4 non-hematologic adverse events, early deaths, and treatment-related deaths are defined as serious adverse events which are reported in semi-annual Monitoring Report with patient registry numbers and details.

In addition, the incidence of Grade 4 non-hematologic adverse events, early deaths, and treatment-related deaths will be calculated for all treated patients when comparing efficacy analyses between arms.

Exact confidence intervals for the proportion is calculated.

Neither of these is judged based on statistical tests, but comparisons are made between arms using Fisher's exact test, as appropriate.

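### The 2021/6 final-analysis note adds an eligibility condition to the safety population that Section 3 of the SAP does not contain, and gives no reason

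*SAP*

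**What the plan says.** Section 3.1 calculates worst-grade adverse event frequencies by group, "using the number of all treated patients as a denominator". Section 3.2 says that the incidence of Grade 4 non-hematologic events, early deaths and treatment-related deaths "will be calculated for all treated patients when comparing efficacy analyses between arms". Neither section mentions eligibility.

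For the final analysis, Section 6.2 gives the methods as "The same as those detailed in Section 2 to 4 in the SAP", so the Section 3 denominator applies there.

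The supplemental note for the final analysis (2021/6) refers back to Section 3 for its safety population, but states: "Safety analyses are performed on 164 eligible and treated patients". It also reports that "OS and PFS are analyzed for all enrolled 170 patients", and names as supportive populations "all eligible 166 patients and 152 patients eligible for centrally pathological review".

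The supplemental note for the first interim analysis (2017/9) put no eligibility condition on safety: "safety analyses are performed on 72 patients whose CRF for treatment are collected by March 31, 2017".

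**The concern.** Two definitions of the same analysis set stand in one document, and they can give different denominators. The phrase in Section 3 is unlikely to be shorthand for eligible and treated, because the SAP writes the eligibility condition out where it wants one: in the response-rate definition (Section 2.3.1) and in the supplementary OS and PFS analyses (Sections 2.1.3 and 2.2.4). Section 3 leaves it out, and so does the interim note. It first appears in the 2021/6 note, which neither gives a reason nor says that Section 3 is amended. The same note does give a reason when it confirms the stratification factor.

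A toxicity rate is meant to describe everyone exposed to the treatment. If an ineligible patient was treated and had a serious event, the note's rule removes both the patient and the event from the final proportion. Common toxicities would barely be affected. Rare and severe events, which Section 3.2 singles out, are where one patient is visible. Section 3.1 also uses these rates to look at differences in toxicity between the arms, and a single event weighs more within an arm than in the pooled set.

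**Working it through.** **Inputs**, all from the 2021/6 note: 170 enrolled, 166 eligible, 164 eligible and treated. The number of ineligible patients who were treated, k, is not given.

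**Counts**
- Ineligible: 170 − 166 = 4. All four are outside the safety set, treated or not.
- Eligible but not in the safety set, read as untreated: 166 − 164 = 2.
- Enrolled but outside the safety set: 170 − 164 = 6 = 4 + 2.

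The 164 is consistent with these counts. It cannot be derived independently, because the total number treated is not stated.

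**Denominator under Section 3**

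N = 164 + k, with k from 0 to 4, so N runs from 164 to 168. The largest share of exposed patients lost is 4/168 = 2.4%. If k = 0, nothing changes.

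**Effect on a rate**

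Let x be the number of events among the 164, and j the number among the k omitted patients (0 ≤ j ≤ k). The reported rate is x/164 and the all-treated rate is (x + j)/(164 + k). The document gives no event counts, so the values of x are illustrative.

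| x | Reported, x/164 | k = 1, with event | k = 4, none with event | k = 4, all with event |
|---|---|---|---|---|
| 0 | 0.00% | 0.61% | 0.00% | 2.38% |
| 2 | 1.22% | 1.82% | 1.19% | 3.57% |
| 8 | 4.88% | 5.45% | 4.76% | 7.14% |
| 82 | 50.00% | 50.30% | 48.81% | 51.19% |

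**One omitted event**

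With k = 1 the shift is (x + 1)/165 − x/164 = (164 − x)/(164 × 165). At x = 0 this is 164/27,060 = 0.61 percentage points. At x = 8 it is 156/27,060 = 0.58. At x = 82 it is 82/27,060 = 0.30. For a rare event the shift is therefore about 0.6 points.

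**Clopper-Pearson 95% intervals for a rare event**
- 0/164: 0% to 2.2%.
- 1/168 (four omitted, one with the event): 0.6%, upper limit 3.3%.
- 4/168 (four omitted, all with the event): 2.4%, 0.7% to 6.0%.

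**Within one arm**

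Treated numbers by arm are not given. Assuming about 82 to 84 per arm, one event is 1/84 = 1.19% to 1/82 = 1.22%, or about 1.2 percentage points of that arm's rate.

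**The case against.** The strongest reply is that no harm is shown. Nothing in the SAP says that any of the four ineligible patients was treated. If none was, 164 is already the all-treated count and only the wording is at fault. The SAP is also an abridged translation, and the discrepancy rests on one short added phrase in a single sentence. The trial's conclusion depends on overall survival in all 170 enrolled patients. Section 3.2 says that the serious-event proportions are not judged by statistical tests. It also has Grade 4 non-hematologic events, early deaths and treatment-related deaths reported by registry number in the semi-annual monitoring reports, with no eligibility condition. A death in an ineligible patient would therefore still be seen within the trial and would still count in OS.

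All of this stands, and it limits the severity. It does not remove the conflict: the reader of the final safety tables is given a population different from the one in Section 3, and cannot tell from the document whether the two coincide.

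A reader might infer more than the document supports:
- *That exposed patients have in fact been dropped.* The rule would drop them, but k is unknown and may be zero.
- *That the ineligible patients were at higher risk, so serious events are understated.* Reasons for ineligibility and event counts are not given. Omitting a patient without the event would slightly raise the reported rate.
- *That the set was narrowed with outcomes in view.* The note was written after the March 2021 follow-up survey and with 151 deaths counted, so independence from outcome cannot be demonstrated from the text. Nothing in it points to selection, and the note states its population and number openly.
- *That cisplatin dose intensity is narrowed too.* Section 4.1 already uses all treated patients, Section 6.2 keeps it, and the note does not touch it.

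**Conclusion.** The inconsistency is real, and the note is wrong as worded when set against Sections 3.1, 3.2 and 6.2. Its numerical effect is bounded and possibly nil: a denominator between 164 and 168, with at most 2.4% of exposed patients omitted. One omitted rare event would move the pooled rate by about 0.6 percentage points. A toxicity near 50% would move by about 1.2 points either way at the extreme.

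These bounds assume that the two eligible patients outside the set were untreated and that the printed counts are correct. The event numbers are illustrations, not data. The overall survival conclusion is unaffected. Severity is moderate to low: it should be corrected because the remedy is simple and the serious-event rates should cover everyone treated, but it does not threaten the trial's main result.

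**What to change.** Check the sentence against the Japanese original first. If the eligibility condition is there, replace it in the 2021/6 note with: *Safety analyses are performed on all treated patients regardless of eligibility.* State the resulting number by arm, which is 164 plus however many of the four ineligible patients were treated. Show the eligible-and-treated set only as a supplementary table, if it is wanted.

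If none of the four was treated, the note should say so. The number 164 then stands and no table changes. Section 4.1 needs no change.

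The cost is one sentence and, if any ineligible patient was treated, a rerun of the safety tables with those patients' safety data included.
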